#### Secondary outcomes

Secondary outcomes will include physiological parameters: blood pressure, heart rate, oxygen saturation at T0, T1, and T2, adverse effects, and satisfaction investigated by a 5-point satisfaction scale (5, very satisfied; 4, satisfied; 3, uncertain; 2, dissatisfied; 1, very dissatisfied) from both patients and therapists, KSS, and the time for ROM ≥ 90°(ROM will be measured by a goniometer). Rescue analgesia should also be an indicator and recorded.

#### Adverse effects and emergency measures

Respiratory adverse effects, such as desaturation (pulse oximetric saturation≦ 94%), arterial hypotension or bradycardia—as well as hallucination and gastrointestinal adverse effects (nausea, vomiting) or any other discomfort—will be evaluated and recorded during and after the procedure. If any of these happen, patients will be given oxygen inhalation, and the discomfort should vanish within 5 min.

### Sample size determination

Pain relief was defined as a 30% decrease in the pain level in T1-T0  [26]. Based on our preceding study on burn-dressing pain and cancer breakthrough pain [24, 25, 27], we hypothesize that pain relief for 80% of the patients in the nitrous oxide/oxygen intervention group, and 20% of the patients in the placebo control group will be classified as successful. With the threshold for statistical significance set at a *P* value of 0.05 (two-sided alpha), these calculations show that 14 patients are needed (seven per group). We finally decided on a sample size of 140 to meet the Chinese Food and Drug Administration standard for feasibility and the safety of staffs in implementing this analgesic [25, 28].

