Orally administered analgesics are often the main treatment in the immediate- to short-term postoperative period. Despite the effectiveness of opioids, they often lead to some undesirable side effects such as vomiting, constipation, and respiratory depression [10]. It is reported that continuous femoral nerve block (CFNB) with local anesthetics could provide superior analgesia and fewer side effects compared with systemic opioids, thus promoting exercises to increase the knee’s range of motion. Nevertheless, a drawback of CFNB is that it can cause a temporary, reversible weakness that accentuates that already caused by TKA and a subsequent increased risk of falling, thus delaying the ability to move [10, 11]. Nitrous oxide, which has been known as an analgesic gas for more than two centuries, is an effective, fast, safe, and noninvasive form of pain relief in the rehabilitation of patients. Different trials have confirmed that the use of nitrous oxide/oxygen can lead to obvious pain relief in different areas of medicine such as labor, colonoscopy, percutaneous liver biopsy, transrectal biopsy of the prostatic gland, migraine, skin laceration repair, venous cannulation, and dentistry [12–18]. The working mechanism of nitrous oxide/oxygen reported by Emmanouil et al. and Carbajal et al. [19, 20] is that it can stimulate neuronal release of endogenous opioid peptides and activate opioid receptors, aminobutyric acid type A (GABA), and noradrenergic pathways. The anxiolytic and sedative effects resemble those of benzodiazepines. Nitrous oxide hardly dissolves in blood and cannot bind to hemoglobin, acts swiftly and is metabolized by the lungs after inhalation ceases [21]. In 1961, Tunstall developed a stable mixture of nitrous oxide and oxygen for pain relief during childbirth. The two gases were mixed in equal proportions and stored in a single cylinder [22]. Soon, the analgesic use of this gas mixture spread over other settings, such as the dental office, prehospital emergencies, etc. In France, the gas mixture was used only in prehospital care and in some labor rooms, and later in procedure-related pain for children [23]. The mixture could play the same role as at least a 15-mg dose of morphine given intramuscularly [16]. It has been observed that all side effects (nausea, vomiting, dizziness) were transient and vanished within 5 min after removing the inhalation device. No serious side effects were noted [23]. However, this new kind of analgesic has not been accepted all over the world. It is mainly used in developed regions including Britain, Australia, and South Africa. In China, it was firstly used in obstetrics, and later in burns surgery [24]. The apparatus is cheap and portable, but most important is that it is easy for patients to control the device. However, its use in TKA postoperative exercise pain control is rarely reported. This study postulates that a nitrous oxide/oxygen mixture can alleviate the pain level to a certain degree, though not absolutely eliminate the pain of rehabilitative exercise.

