Recent worst pain (during functional exercise) reported to be 4 or higher (on a Numerical Rating Scale (NRS) of 0 to 10)	Disease involving ear, nose, larynx, such as sinuses, otitis media

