### Procedure

All the procedures will be carried out in the rehabilitation department. All the patients will be recruited on the basis of being without any other analgesic before this study. The patients will inhale the premixed nitrous oxide/oxygen or placebo gas through a close-fitting mask for 2 min before exercise and throughout the whole process. They will be continuously monitored with a pulse oximeter during the whole process, and blood pressure will be taken before, during and after each functional exercise session. The inhaled mixture will be administered by the patients themselves (Fig. 2). Neither the therapists nor the patients know which gas mixture will be contained in each gas holder. During the functional exercise, the patients will inhale the gas mixture continuously. The inhalation of the gas mixture will be stopped when the functional exercise ends.

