### Measures

The following parameters will be recorded by the performer: age, sex, baseline pain score, blood pressure, heart rate, and oxygen saturation of blood monitored using Infinity Delta XL (Draeger Medial Systems Inc., Danvers, Shanghai, China) [25]. During mixture inhalation, pulse oximetry monitoring will not be necessary because the patients breathe 50% oxygen resulting in hyperoxemia, and the diffusion hypoxia phenomenon does not appear in this type of nitrous oxide use. For safety, we will measure oxygen saturation. Patients will rate their knee pain on the operated side with a numerical rating scale with endpoints of 0 (no pain) and 10 (worst pain tolerable) during flexing [23]. Pain severity, blood pressure, heart rate and oxygen saturation of blood will be monitored immediately after functional exercise begins (T0), 5 min (T1) after the beginning of functional exercise, and 5 min (T2) after functional exercise finishes. Both patients’ and therapists’ satisfaction with pain control under the new analgesia will be investigated by a 5-point satisfaction scale (5, very satisfied; 4, satisfied; 3, uncertain; 2, dissatisfied; 1, very dissatisfied). The KSS [11] will be obtained by questionnaire. According to our previous qualitative study, one of the substantial indicators of discharging from hospital for TKA patients is knee range of motion (ROM) ≥ 90°. Thus, the postoperative knee ROM will be measured by goniometer, and the time to reach ROM ≥ 90° will also be recorded. Moreover, adverse effects, and rescue analgesic need should be recorded and compared.

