### Outcome measures

#### Primary outcome

The primary endpoint measures will be pain severity at T0, T1, and T2. The anticipated pain score (Numerical Rating Scale; NRS) during functional exercise will be a reduction from to 3 to 5 in the intervention group. Repeated-measures analysis of variance will be used for data analysis.

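### The 30% pain-relief rule takes T0 as its reference, but T0 is scored after at least 2 minutes of gas, so the responder rate may miss part or all of the effect

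*Protocol article*

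**What the plan says.** Four statements in the protocol article fix the timing.

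- Procedure: the gas is inhaled "through a close-fitting mask for 2 min before exercise and throughout the whole process". It stops when the exercise ends.
- Measures: pain is "monitored immediately after functional exercise begins (T0), 5 min (T1) after the beginning of functional exercise, and 5 min (T2) after functional exercise finishes".
- Sample size determination: "Pain relief was defined as a 30% decrease in the pain level in T1-T0". This rule underlies the assumed success rates of 80% and 20%.
- Primary outcome: "The primary endpoint measures will be pain severity at T0, T1, and T2", analysed by repeated-measures analysis of variance. T0 is thus also an outcome.

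Two other pain scores are mentioned. Measures lists "age, sex, baseline pain score, blood pressure, heart rate, and oxygen saturation of blood" among the recorded items, without saying when the pain score is taken or during what activity. Table 1 requires "Recent worst pain (during functional exercise) reported to be 4 or higher" for entry. The 30% rule uses neither of them. On onset, the Background says only that nitrous oxide "acts swiftly and is metabolized by the lungs after inhalation ceases".

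**The concern.** A change score measures a treatment effect only if its reference is free of treatment. Here T0 falls at least 2 minutes into inhalation and T1 about 7 minutes into it. T1-T0 therefore captures only what is gained between those two moments. If the gas acts as fast as the Background suggests, some relief is already present at T0, and only in the nitrous oxide arm. The faster the onset, the fewer patients meet the 30% rule for the same true relief at T1.

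At stake is the meaning of the responder rate, and of any other result expressed as change from T0 or adjusted for T0 as though it were a baseline.

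**Working it through.** **1. The plan's own figure.** Inputs from the sample size section: p1 = 0.80, p2 = 0.20, two-sided alpha 0.05. Power is not stated; 80% is assumed.

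n per group = (z₀.₉₇₅ + z₀.₈₀)² × [p1(1−p1) + p2(1−p2)] / (p1−p2)² = (1.960 + 0.842)² × 0.32 / 0.36 = 6.98, rounded up to 7.

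This matches the stated 7 per group and 14 in total. (The pooled-variance formula would give 10 per group.) The arithmetic is not at fault. A different reference point changes what the 80% and 20% mean, not the 14.

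**2. Timeline from the start of gas.**

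| Reading | Minutes of gas | Status |
|---|---|---|
| Before mask | 0 | no score used in the 30% rule |
| T0 | at least 2 | on treatment |
| T1 | about 7 | on treatment |
| T2 | 5 min after exercise and gas stop | off gas |

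**3. One patient.** Let e be the true proportional reduction at T1 and f the share of it present at T0. The fall seen from T0 to T1 is 1 − (1−e)/(1−f·e). Take untreated exercise pain of 7 and e = 0.40, so T1 = 4.2.

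- f = 0: T0 = 7.0, fall 40%, responder.
- f = 0.5: T0 = 5.6, fall 25%, non-responder.
- f = 1: T0 = 4.2, fall 0%.

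Setting the fall to 30% gives the tipping share f = [1 − (1−e)/0.7]/e. This is 0.36 for e = 0.40 and 0.57 for e = 0.50.

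**4. Responder rates by simulation.** All inputs are assumptions: untreated exercise NRS mean 6, SD 1.8, within-patient correlation 0.6, scores rounded and limited to 0–10, 400,000 draws per case. The control rate is 11%. Power is for the responder comparison with 70 per arm, that is 140 at 1:1.

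| Share present at T0 | Responders, e = 50% | Power | Responders, e = 40% | Power |
|---|---|---|---|---|
| 0% | 87% | >99% | 70% | >99% |
| 25% | 76% | >99% | 57% | >99% |
| 50% | 57% | >99% | 41% | 98% |
| 75% | 33% | 89% | 25% | 56% |
| 100% | 16% | about 12–13% | 13% | 5% |

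**5. A second model, built on the plan's 80% and 20%.** Assume these are the true rates against pre-gas pain, and that percentage reduction is normal with SD 20 points. The means are then 30 ± 0.842 × 20 = 46.8 and 13.2 points, a drug effect of 33.7 points before rounding. The control rate is held at 20%. A nitrous oxide patient counts as a responder if the reduction is at least 1 − 0.7(1 − 0.337f). For f = 0, 25, 50, 75 and 100% the responder rate is 80, 71, 60, 48 and 37%. Power with 70 per arm is above 99.9% for the first two, then 99.9, 95 and 60%.

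**6. The planned ANOVA.** In the model of step 4 with e = 50%, the mean difference between arms is 3f points at T0 and 3 points at T1. Averaged over the two it is (3f + 3)/2, which rises from 1.5 to 3.0 points as f goes from 0 to 1. The T1 difference is 3 points whatever f is, a standardised difference of about 2.1, with power near 1 at 70 per arm. Only the T0-to-T1 contrast, 3 − 3f points, shrinks to zero.

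**The case against.** The strongest reply is that the 30% rule appears only in the sample size section. The primary endpoint is pain at all three times, with T0 as an outcome, and no section makes change from T0 an analysis endpoint. The total was raised from 14 to 140 for other reasons. All of this stands, and it limits the point.

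It also rules out several stronger readings.

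- **That the primary analysis is biased towards no effect, so a fast gas could be declared ineffective.** The group main effect grows with faster onset (step 6), and the comparison at T1 does not depend on T0. The article does not say which ANOVA term decides, so it does not support the claim that the trial tests change from T0.
- **That the group-by-time test is lost.** The interaction has three levels. If relief is present at T0 and T1 and fades by T2, off gas, the interaction can still show it.
- **That T0 cancels the effect entirely.** The article describes onset only as swift, with no minutes. The share may be part or all.
- **That a T0 of 0 makes the percentage undefined.** True, but this is 0.1 to 0.3% of draws in the model of step 4.
- **That two suitable baselines already exist.** The recorded baseline score has no stated time or activity. The eligibility score is a recalled worst value selected at 4 or higher. Set against a momentary T1 score, it would favour falls in both arms through the worst-versus-current difference and regression to the mean.

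The reply does not repair the definition. The article states the rule outright and the gas schedule contradicts its use of T0 as a baseline, so this is not a detail left to a fuller document.

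**Conclusion.** The point holds in limited form. The reference for the 30% rule is an on-treatment score. That follows from the Procedure, Measures and sample size sections alone, and no other section corrects it. The responder rate, and any change-from-T0 or T0-adjusted result, may understate the effect by an unknown amount.

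The size rests on assumed score distributions and on the unknown share of effect present at T0. With half of it present, responders fall from 87% to 57% (or from 70% to 41% for a true 40% reduction), but power at 70 per arm stays at 98% or more. With three quarters present, power is 89% or 56% in the first model and 95% in the second. Only when nearly all is present does it collapse in the first model; the second still gives 60%. At the planned size the main harm is therefore to what the responder rate means. This should be fixed, but it does not invalidate the primary analysis.

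**What to change.** 1. State that T0 is an on-treatment outcome and is never used as a baseline or covariate.
2. Base the efficacy conclusion on the between-arm difference in NRS during gas, at T1 or at T0 and T1 together, adjusted for the baseline pain score.
3. Define the 30% responder as a fall from an exercise-pain NRS recorded at a stated time before the mask is applied. The baseline score listed under Measures can serve once its time and activity are fixed. The recalled worst-pain eligibility score should not be used.

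The cost is wording and, at most, one timed NRS reading per patient, if the present baseline score is not exercise pain taken before the mask. The gas schedule, the calculated 14 and the planned 140 do not change.

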### Data Safety and Monitoring Board (DSMB)

A DSMB will be established shortly after the project launch and will meet several times during the data collection period. Members will included two pain management specialists; four professional therapists and nursing officers; and a senior academic statistician who served as the Board’s Chair.

### Data analysis

Before the study, all data collectors will be given unified training. The data will be analyzed using SPSS Statistics for Windows, Version 22.0. Chicago, IL, USA. Descriptive statistics will be analyzed by medians (inter-quartile ranges), means (standard deviations), and proportions (exact binomial 95% confidence intervals). The baseline parameters will be compared between the two groups (“control” and “experimental”) using the chi^2^ test or Fisher’s exact test for categorical variables and the Mann-Whitney *U* test for non-parametric data. Statistical significance will be defined as *P* < 0.05.

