### Randomization and blinding

According to the computer-generated random number table in a 1:1 ratio, all the participants will be randomized to the intervention group (conventional treatment plus nitrous oxide/oxygen) or the control group (conventional treatment plus oxygen). The allocation sequence of each patient will be decided by a computer-generated schedule, which will be numbered by a statistician. The randomization schedule will be kept and sealed in an independent research room. Apart from the project manager, who is responsible for gas distribution, no other nurses or data collectors will have access to the data allocation. Prior to, and during, the treatment period, the participants, therapists, and the investigators will all be blind to the allocation. Only the project manager will know the allocation. The two gases will be stored in identical-looking canisters labeled A and B (Additional file 2). Patients given the letter A will be treated using a canister with the appropriate letter containing premixed nitrous oxide/oxygen. Those with letter B will be given oxygen only.

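### Baseline pain is recorded, but its only stated use is between-arm significance testing; the primary ANOVA names no baseline term, and T0, taken on gas, cannot act as one

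*Protocol article*

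**What the plan says.** All references are to the protocol article.

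- **Measures:** "The following parameters will be recorded by the performer: age, sex, baseline pain score". Blood pressure, heart rate and oxygen saturation are on the same list. The time at which the baseline pain score is taken is not given.
- **Table 1:** entry requires "Recent worst pain (during functional exercise) reported to be 4 or higher" on the 0 to 10 NRS. Every randomized patient therefore has at least one exercise-pain rating from before the study gas.
- **Data analysis:** "The baseline parameters will be compared between the two groups", with chi-square or Fisher tests for categorical variables, Mann-Whitney tests for non-parametric data, and significance at P < 0.05. No other use of baseline data is stated.
- **Primary outcome:** pain severity at T0, T1 and T2. "Repeated-measures analysis of variance will be used for data analysis". No factor, contrast or covariate is named.
- **Procedure and Measures:** gas is inhaled for 2 min before exercise and throughout it. T0 is taken immediately after exercise begins.
- **Randomization and blinding:** allocation follows a "computer-generated random number table in a 1:1 ratio".

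**The concern.** Two things are at issue.

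First, the baseline tests answer no useful question. With properly randomized arms, any baseline difference is due to chance. A non-significant P value does not show that an imbalance is harmless, and a significant one leaves the analyst to decide afterwards whether to adjust.

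Second, pre-treatment pain may well predict pain during the treated session, yet the stated primary analysis gives it no role. Including T0 in the repeated-measures model may look like baseline adjustment, but T0 is measured on gas, so all three scores in the model are post-treatment. Using T0 as the covariate would be worse than using none, since it could absorb part of the effect under study.

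At stake are the width of the interval around the between-group pain difference and its sensitivity to a chance imbalance in baseline pain.

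**Working it through.** **The plan's own figure.** Sample size determination assumes "pain relief for 80% of the patients in the nitrous oxide/oxygen intervention group" and that "20% of the patients in the placebo control group will be classified as successful", with two-sided alpha 0.05, and arrives at 7 per group. Power is not stated. With 80% assumed and the unpooled formula:

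n per group = (0.8×0.2 + 0.2×0.8) × (1.960 + 0.842)² / (0.8 − 0.2)² = 0.32 × 7.85 / 0.36 = 6.98, so 7 per group and 14 in all.

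This reproduces the stated figure. The planned 140 was then chosen on other grounds. With 70 per group, power for 80% against 20% exceeds 99.9%.

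**Inputs for the precision check.** N = 140, 70 per arm (document). The correlation r between baseline pain and later pain is not in the documents, so 0.3, 0.5 and 0.7 are assumed.

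**One time point (for example T1).** Adjusting for baseline multiplies the variance of the group difference by 1 − r², and the CI width by √(1 − r²). The equivalent unadjusted sample size is 140/(1 − r²).

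| r | Variance factor | CI narrower by | 140 adjusted equals, unadjusted |
|---|---|---|---|
| 0.3 | 0.91 | 5% | 154 |
| 0.5 | 0.75 | 13% | 187 |
| 0.7 | 0.51 | 29% | 275 |

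**Group effect averaged over T0 to T2.** Assume also that all pairs of scores share the same correlation r. The unadjusted variance is then proportional to (1 + 2r)/3 and the adjusted variance to (1 + 2r)/3 − r².

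- r = 0.3: (0.533 − 0.09)/0.533 = 0.83, equivalent to about 168 patients
- r = 0.5: (0.667 − 0.25)/0.667 = 0.63, about 224
- r = 0.7: (0.80 − 0.49)/0.80 = 0.39, about 361

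**Group-by-time contrast (T1 − T0).** Under the same assumption the covariance of baseline with T1 − T0 is r − r = 0, so the covariate explains nothing. A simulation of 3,000 trials per value of r, with 70 per arm, gave variance ratios of 1.00 to 1.01.

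**What a baseline test can miss.** If baseline and outcome have equal SDs, a baseline difference of k standard errors shifts the unadjusted outcome difference by about r × k standard errors. An imbalance just short of P < 0.05 (k = 1.96) would pass the test. It would still move the result by 1.96 × 0.3 = 0.59, 1.96 × 0.5 = 0.98 or 1.96 × 0.7 = 1.37 standard errors.

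**The case against.** The strongest reply is that the primary method is one sentence in a journal article. It names no covariate, but it excludes none, and model terms are often left to an analysis plan that is not shown. A reader might infer that the trial has committed to an unadjusted analysis; the text does not support that. What stands is narrower: the article does state a use for baseline data, and the use it states is significance testing.

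A reader might also infer that the trial is underpowered without adjustment. The documents do not support this either. Power is above 99.9% on the protocol's own responder assumption. For the NRS comparison no SD or target difference between arms is given from which power could be computed.

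The gain also depends on the effect tested. The protocol does not say whether that is the group effect or group by time, and its definition of pain relief uses the T1 − T0 change, for which a baseline covariate adds nothing. That point stands. On the other side, a change from T0 subtracts whatever effect the gas already has at T0, whereas the between-group level comparison keeps it.

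Further, the entry floor of 4 restricts the range and may lower r, so the upper end of the table may be optimistic. An unadjusted comparison of randomized arms is valid, and its interval already allows for chance imbalance over repeated trials. Adjustment improves precision and corrects for the imbalance actually observed. Finally, nothing in the article says that baseline P values will guide later adjustment; that is a risk of the practice, not a stated plan.

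**Conclusion.** The point holds as one of efficiency and reporting. The only stated use of baseline data is a test that is uninformative after randomization, the primary ANOVA names no baseline term, and T0 cannot stand in for one.

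For a between-group comparison at one time point, adjustment would narrow the CI by about 5% to 29% over the assumed range of r from 0.3 to 0.7. The gain is larger for the T0 to T2 average if correlations are equal, and there is none for the group-by-time contrast. The size rests wholly on an assumed correlation. The validity of the trial and its power on the stated responder assumption are not in question. The change is worth making because a pre-gas pain rating is already collected at screening.

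**What to change.** 1. Name a pain score obtained before any gas as a covariate in an ANCOVA or mixed model for the between-group NRS comparison. Use the recorded baseline pain score if it is taken before gas, otherwise the screening worst exercise-pain NRS. State when the baseline score is taken. Do not use T0 as the covariate.
2. Report the adjusted mean difference with its 95% CI.
3. Show baseline values by arm without P values.
4. Adjust blood pressure and heart rate only for readings taken before gas starts. The article says blood pressure is taken before each session, but a pre-exercise reading may fall within the 2 min of inhalation.

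The cost is wording in the analysis plan, fixed before unblinding. The pain covariate needs no new measurement, since the screening NRS exists for every patient. Its strength as a predictor is unknown. For blood pressure and heart rate, the timing of the first reading has to be confirmed.
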